**Symptoms (What number would you give your …symptom… on a scale of 0 to 10?**												
No pain	0	1	2	3	4	5	6	7	8	9	10	Much pain
No fatigue												Very fatigue
Not short of breath												Very short of breath
Not obstipated												Very obstipated
Not sad												Very sad
Not anxious												Very anxious

The Consumer Quality Index Palliative Care (CQ Index) is a validated questionnaire assessing quality indicators from the perspective of patients and bereaved relatives [21,22]. The quality indicators measured by this CQ Index are also directly related to the key objectives of the National Quality Improvement Programme (see Table 2). CQ index questions for instance concern patients’ or bereaved relatives’ experiences regarding the control over palliative care, the coordination of palliative care, the concordance between the care given and needs, preferences and values, and the physical, psychosocial and spiritual care received. In the version for bereaved relatives, questions are also asked about the actual and preferred place of death of the patient. The questionnaire version for patients consists of 56 items, while the version for bereaved relatives consists of 64 questions. Both questionnaire versions take approximately 30–45 minutes to complete. For inpatient patients, the questionnaire will be completed on the basis of an interview with a trained interviewer. Patients who receive care at home and bereaved relatives will receive the questionnaire by post to be completed and returned in a reply envelope to the research team. No reminders will be sent to non-responding patients, while a reminder will be sent after two weeks to non-responding bereaved relatives.

**Table 2 T2:** Key objectives of the national quality improvement program and associated quality indicators, measured with the CQ index palliative care

**Key objectives of the programme**	**Quality indicators measured with CQ index version for patients**	**Quality indicators measured with CQ index version for bereaved relatives**
Patients die at their preferred place	-	*Percentage of patients who died in the location of their preference
		*Extent to which patients in the last month before their death were in the location of their preference
Patients and relatives feel they are in control regarding palliative care	*Extent to which patients experience respect for their autonomy	*Extent to which relatives indicate that the patient was asked about her/his opinions with regard to end-of-life decisions
	*Extent to which patients receive information from their caregivers about the expected course of the disease	*Extent to which direct relatives received information about the advantages and disadvantages of various types of treatment
	*Extent to which patients receive information about the advantages and disadvantages of various types of treatments	*Extent to which direct relatives received information that was understandable and unambiguous at the time of the patient’s death
	*Extent to which patients indicate that they receive understandable explanations	*Extent to which, according to the bereaved relatives, their autonomy was respected
		*Extent to which direct relatives were informed about the possibilities of aftercare
Patients and relatives see palliative care as being coordinated	*Extent to which patients know who the contact person is for the care	*Extent to which the bereaved relatives knew who the contact person was for the care
	*Extent to which patients experience expertise of caregivers and continuity of care	*Extent to which direct relatives perceived expertise of caregivers and continuity of care
	*Extent to which patients receive contradictory information	
Patients and relatives feel care to be concordant with their needs, preferences and values	*Extent to which patients are satisfied with “politeness” and “being taken seriously” by caregivers	*Extent to which the direct relatives felt that they were treated well in all respects by the caregivers
	*Extent to which patients experience respect for their privacy	*Extent to which direct relatives considered that the patient had the opportunity to be alone
	*Extent to which patients indicate that caregivers respect their life stance	*Extent to which the direct relatives had the opportunity to be alone with their relative
	*Percentage of patients who receive medical aids soon enough	
Patients and relatives receive care for their needs in the physical, psychosocial, and spiritual domains	*Extent to which patients receive support for their physical symptoms (pain, fatigue, shortness of breath and constipation)	*Extent to which relatives indicate that the patient had access to a counselor for spiritual problems
	*Extent to which patients receive help with physical care	*Extent to which relatives indicate that the patient received support with preparations for saying goodbye
	*Extent to which patients receive attention from their caregivers	*Extent to which relatives indicate that there was attention for the psychosocial and spiritual well-being of the patient
	*Extent to which patients receive support when they feel anxious or feel depressed	*Extent to which, according to the direct relatives, attention was paid to their own psychosocial and spiritual well-being
	*Extent to which patients indicate that they have access to a counsellor for spiritual problems	*Extent to which direct relatives felt supported by the caregivers immediately after the patient’s death
		*Extent to which a final conversation or discussion was held to evaluate the care and treatment

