**Methods/Design:**

This paper presents the protocol of the evaluation study consisting of a quantitative effect evaluation and a qualitative process evaluation. The effect evaluation has a pre-test post-test design, with measurements before implementation (month 0) and after implementation (month 9) of a best practice. Patients are eligible if they have a life expectancy of less than six months and/or if they are undergoing palliative treatment and provided they are physically and mentally capable of responding to questionnaires. Bereaved relatives are eligible if they have been involved in the care of a deceased patient who died after a sickbed between six weeks and six months ago. Three types of measurement instruments are used: (1) numerical rating scales for six symptoms (pain, fatigue, breathlessness, obstipation, sadness and anxiety), (2) the Consumer Quality Index Palliative Care - patient version and (3) the version for bereaved relatives.

The process evaluation consists of analysing implementation plans and reports of the implementation, and individual and group interviews with healthcare professionals. This will be done nine to eleven months after the start of the implementation of a best practice.

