### Effect evaluation

Pre-test and post-test measurements will take place in the effect evaluation, in month 0 and month 9 respectively (see Figure 2). During these two measurement months, eligible patients and bereaved relatives will be asked to participate.

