#### Data collection

In the pre-test and post-test measurements, a set of quality indicators will be measured [20], making use of three types of measurement instruments:

•Numeric Rating Scales of six symptoms

•The Consumer Quality Index Palliative Care for patients

•The Consumer Quality Index Palliative Care for bereaved relatives

Numeric Rating Scales (NRS) will be used to measure the quality indicators ‘The % of patients with moderate to severe pain’, ‘The % of patients with moderate to severe fatigue’, ‘The % of patients with moderate to severe shortness of breath’, ‘The % of patients with moderate to severe constipation’, ‘The % of patients with moderate to severe anxiety’ and ‘The % of patients who feel moderately to severely depressed’. These indicators are associated with one specific programme objective, namely ‘Patients receive care for their needs in the physical and psychosocial domains’.

Patients will be reminded by one of their health care professionals to complete the NRS for the six symptoms (see Table 1) approximately the same time at three consecutive days. In principle, the patient will fill in the NRS scores. Only if the patient is not able to write will the health care professional assist the patient by writing down the NRS scores. The completed NRS forms will be collected by the health care professional after day 3 and send to the research team at the end of the measurement period.

**Table 1 T1:** Numeric rating scales of 6 symptoms

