#### Data analysis

Descriptive statistics (frequencies, percentages and means) will be used to analyse background characteristics.

The effects of the separate implementation trajectories (research question 2) will be analysed using descriptive analyses as well as univariate analyses (with paired t tests or McNemar’s test). To assess the differences between pre-test and post-test measurements for the whole programme (research question 1), multilevel analysis will be used, including the levels of the participating care networks or care organizations, and the type of best practice. SPSS, STATA and ML-WIN will be used for the statistical analysis.

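### Patient CQ Index: collection mode is tied to care setting and neither is in the stated analysis, so a change in the inpatient/home mix between waves can pass for a programme effect

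*Protocol article*

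**What the plan says.** Under Effect evaluation, Data collection, the protocol article sets the collection rule for the CQ Index by place of care. For one group, "For inpatient patients, the questionnaire will be completed on the basis of an interview with a trained interviewer". For the others, "Patients who receive care at home and bereaved relatives will receive the questionnaire by post". On follow-up of non-responders: "No reminders will be sent to non-responding patients, while a reminder will be sent after two weeks to non-responding bereaved relatives". The Ethical considerations section confirms the split: inpatients give written consent for this questionnaire because an interviewer completes it, and home patients do not need to.

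Recruitment is described by wave: "During these two measurement months, eligible patients and bereaved relatives will be asked to participate". No quota or balance by setting is stated. The Study population section says that, in trajectories with more than five organisations, the organisations sampled should cover all the settings involved, so one trajectory can contain both inpatients and home patients.

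The Data analysis section gives descriptive and univariate analyses (paired t or McNemar tests) for each trajectory. For the whole programme it gives a multilevel model "including the levels of the participating care networks or care organizations, and the type of best practice". Neither setting nor mode of collection is named.

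**The concern.** The patient CQ Index result is a difference between two waves with no comparison group. Inpatient and home respondents differ in how the form is completed, whether an interviewer is present, the consent step and how non-return arises. They may also differ in illness and in the care received. All of these move together with setting. If the share of inpatients among respondents is not the same at month 0 and month 9, the pre-post difference contains a component that has nothing to do with the best practice, and no control group would reveal it.

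At programme level this could add to or mask a real change. At trajectory level, with 15 to 20 patients per wave, the mix will vary by chance, and the resulting figures go into the feedback reports that organisations may act on.

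**Working it through.** **The plan's own figure.** 17 trajectories × 2 waves × 15 patients = 510 patients per year, and × 4 years = 2040. Both match the article. Each wave therefore has 17 × 15 × 4 = 1020 patients at the minimum target. The article gives no effect size, standard deviation or power, so there is no power calculation to reproduce.

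**Form of the bias.** Let p0 and p9 be the inpatient shares among respondents at the two waves, and d the difference in mean score between interviewed inpatients and postal home patients, in SD. With no true change, the mean at each wave is the home mean plus p × d, so

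spurious pre-post difference = (p9 − p0) × d.

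This is zero if the mix is stable or if d is zero.

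**Programme level.** SE = √(1/1020 + 1/1020) = 0.0443 SD. This takes patients as independent; variation between clusters in their change over time would enlarge it. A difference of 1.96 × 0.0443 = 0.087 SD would reach two-sided p = 0.05. Both d and the shift below are assumptions. The false-positive rate is 1 − Φ(1.96 − b/SE) + Φ(−1.96 − b/SE), with b the bias and a nominal 5%.

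| Shift in mix | d (SD) | Bias (SD) | Bias/SE | False-positive rate |
|---|---|---|---|---|
| 0 points | any | 0 | 0 | 5% |
| 10 points | 0.2 | 0.02 | 0.45 | 7.4% |
| 10 points | 0.3 | 0.03 | 0.68 | 10.4% |
| 20 points | 0.3 | 0.06 | 1.35 | 27% |
| 20 points | 0.4 | 0.08 | 1.81 | 44% |

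At the upper target of 20 patients, each wave has 20 × 17 × 4 = 1360. The SE is then √(2/1360) = 0.038 SD, and the same range of bias is 0.5 to 2.1 SE.

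**One trajectory.** Suppose 8 of 15 are interviewed at one wave and 4 of 15 at the other, with d = 0.3. The bias is (8/15 − 4/15) × 0.3 = 0.08 SD. The unpaired SE is √(2/15) = 0.365 SD, so this is about 0.2 SE. With a true 50:50 split, a gap of at least 4 in 15 arises by chance in about 20% of trajectories (binomial).

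**Does the multilevel structure remove it?** The model level is left open between network and organisation. The expected generalised least-squares estimate was calculated with a true effect of 0, d = 0.5 SD and an inpatient share going from 60% to 40%. The unadjusted artefact is then 0.20 × 0.5 = 0.100 SD. The residual variance was taken as 0.94.

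| Structure | Artefact left (SD) |
|---|---|
| Network or trajectory intercept, both settings inside | 0.100 |
| Organisation intercept, each organisation mixing both settings | 0.100 |
| Organisation intercept, single-setting organisations, between-organisation variance 0.048 | 0.058 |
| The same, variance 0.111 | 0.037 |
| The same, variance 0.30 | 0.018 |

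A random intercept for organisation removes part of the artefact when organisations are single-setting. It removes none when they mix settings or when the network is the level. The univariate trajectory tests have no place for such a term.

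**The case against.** The strongest reply is that the rule does not change over time. Inpatients are interviewed and home patients are posted the form at both waves, and the absence of patient reminders is also constant. With a stable mix everything cancels, and nothing in the article reports or predicts a change in mix. This stands, and the point is therefore conditional on a change in mix.

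A second reply is that a journal article need not list covariates and a full analysis plan may do so. This also stands, and the omission alone is no error. The collection rule and the univariate trajectory tests are stated, however, and mode can be used later only if it is recorded with each form.

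A third reply is that the effect is modest. At the minimum target, the assumed range tops out at 0.08 SD, below the 0.087 SD that would by itself reach significance. In one trajectory it is about a fifth of a standard error, and chance imbalance tends to average out over about 68 trajectories. This is correct, although a bias too small to be significant by itself still shifts the estimate and the false-positive rate.

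A reader might also infer more than the documents support:

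- That interviewed patients answer more favourably or rarely fail to respond, so a move towards home would look like falling quality. The article gives no direction or size for a mode difference.
- That this is a pure measurement fault, present even with identical patients in both waves. Mode is determined by setting, so with the same setting mix the artefact is zero, and a shift in mix would also change case mix and care received.
- That the objective on preferred place of death will itself move the mix. That objective does not imply a move in either direction, and Table 2 shows it measured only through bereaved relatives, who are all surveyed by post.

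**Conclusion.** The point holds in a limited form. For the patient CQ Index, mode is fully tied to setting, the comparison is uncontrolled, no balance by setting is stated, and the stated analyses name neither factor. If the inpatient/home mix of respondents differs between waves, and the two groups score differently for any reason, part of that difference can be read as a programme effect. An organisation-level random intercept would remove some of it at best, and a network level none.

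The illustrative size is 0.45 to 1.8 standard errors of the programme contrast at the minimum target. It rests on assumed values for the score difference and the shift, and on independent patients. Neither assumed value can be checked from the documents. The relatives' version is collected in one way throughout, and the symptom scales are self-completed with help only for patients who cannot write, so neither is in scope. This is a worthwhile and inexpensive improvement to the stated analysis and does not invalidate the design.

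**What to change.** 1. Record mode (interview or post) and care setting for every patient CQ Index form when it is collected.
2. In the programme model for patient CQ Index outcomes, add mode/setting as a fixed term and make organisation a level, settling the present choice between network and organisation.
3. Report the adjusted estimate beside the unadjusted one.
4. Report the setting mix and response rate for each wave, overall and by trajectory. By trajectory this should stay descriptive, because 15 to 20 patients per wave are too few to analyse separately by mode.

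The cost is one variable that staff already know for each form, one model term and a short table, with no added burden on patients. The downside is that mode and setting cannot be separated in these data. The adjusted figure therefore also removes any true effect that acts through a change of setting, which is why both estimates should be shown.

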#### Data analysis

Descriptive statistics (frequencies, percentages and means) will be used to analyse background characteristics.

The effects of the separate implementation trajectories (research question 2) will be analysed using descriptive analyses as well as univariate analyses (with paired t tests or McNemar’s test). To assess the differences between pre-test and post-test measurements for the whole programme (research question 1), multilevel analysis will be used, including the levels of the participating care networks or care organizations, and the type of best practice. SPSS, STATA and ML-WIN will be used for the statistical analysis.

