## Background

Death comes to us all. Nowadays, acute deaths due to infectious diseases have largely been replaced by non-sudden deaths, caused by e.g. cancer, cardiovascular diseases and dementia [1]. Therefore, the need for palliative care is increasing. High-quality palliative care is important in improving the quality of life of patients and their families facing the problems associated with a life-threatening disease [2]. Since the 1990s, the Dutch government has consistently invested in the optimization of palliative care, and nowadays many best practices are available in the Netherlands. 'Best practices' are defined in this paper as practices, often developed among small groups of patients and professionals, that contribute to the improvement of palliative care and that are transferrable to other settings. Some examples of best practices in the Netherlands are:

The Dutch version of the Liverpool Care Pathway for the Dying Patient [3]. The pathway was developed to aid members of a multi-disciplinary team in matters relating to continuing or discontinuation of treatments and regarding comfort measures during the last days and hours of a patient's life.

PaTz – a systematic approach to optimize palliative care based on the Gold Standard Framework (http://www.goldstandardsframework.org.uk/). Its elements include collaborative meetings of general practitioners and community nurses, the timely identification of patients in need of palliative care and the drafting of an advance care plan [4].

Informare, a tailored method that enables health care professionals to provide timely information about palliative care to patients and relatives [4].

‘Signal box for nursing assistants’, a tool that enables nursing assistants to identify palliative care needs in their patients and pass this information on to other professionals [4].

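### The pre-test and post-test samples are separate cross-sections without a control group, but the stated analysis gives background characteristics no part in the effect estimates

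*Protocol article*

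**What the plan says.** The abstract of the protocol article sets out the comparison: "The effect evaluation has a pre-test post-test design, with measurements before implementation (month 0) and after implementation (month 9) of a best practice". No control group is planned. The Effect evaluation section describes recruitment: "During these two measurement months, eligible patients and bereaved relatives will be asked to participate". Following up the month-0 respondents is not mentioned.

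On eligibility the abstract states for patients: "Patients are eligible if they have a life expectancy of less than six months and/or if they are undergoing palliative treatment". Relatives qualify through a "deceased patient who died after a sickbed between six weeks and six months ago".

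The Data analysis section under Effect evaluation makes three statements:
- On respondent characteristics: "Descriptive statistics (frequencies, percentages and means) will be used to analyse background characteristics".
- Each trajectory (research question 2) is analysed descriptively and with univariate paired tests.
- The whole programme (research question 1) is analysed with a multilevel model, for which network or organisation and type of best practice are the only terms named.

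The mode of the CQ Index depends on care setting. "For inpatient patients, the questionnaire will be completed on the basis of an interview with a trained interviewer", whereas patients at home receive it by post.

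**The concern.** When different people are measured before and after, the period difference mixes two things: a change in care, and a change in who answered. Randomisation or a concurrent control would deal with the second, and this design has neither. What remains is adjustment for recorded characteristics, and the stated analysis gives these no role beyond description.

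For patients, the characteristics at issue are age, sex, diagnosis, disease phase and care setting. A change in setting mix would also change the share of CQ Index answers given in an interview. For relatives they are the relationship to the deceased and the time since death.

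The intervention itself could alter the patient sample. The Background section names, as one element of PaTz, "the timely identification of patients in need of palliative care". If PaTz is among the selected practices, the patients recognised as palliative at month 9 may differ from those recognised at month 0. At stake are the primary programme estimate and the trajectory results that go back to care organisations in feedback reports.

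**Working it through.** **1. Head count (Study population section).** About 17 trajectories a year, two periods, four years; minimum 15 patients and 30 relatives per trajectory and period.
- Patients: 17 × 15 × 2 = 510 a year; × 4 = 2040.
- Relatives: 17 × 30 × 2 = 1020 a year; × 4 = 4080.

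The article's figures are reproduced. They count each period's respondents as separate participants. The same people measured twice would be 17 × 15 × 4 = 1020 patients and 17 × 30 × 4 = 2040 relatives.

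**2. Can the same person appear twice?**
- Relatives: six weeks is 42 / 30.44 = 1.38 months. With measurement months running from 0 to 1 and from 9 to 10, eligible deaths fall between −6 and 1 − 1.38 = −0.38 months for the pre-test, and between 9 − 6 = 3 and 10 − 1.38 = 8.62 months for the post-test. The windows do not overlap, so the two samples concern different deaths.
- Patients: a life expectancy under six months is shorter than the nine-month interval. Some patients who qualify through palliative treatment may still be eligible at month 9. The samples are therefore largely, not strictly, different.

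**3. Size of the bias with no true effect.** The documents give no case-mix figures, so every input here is an assumption. Take one symptom indicator on the article's own scale (percentage with moderate to severe symptoms) and two patient groups. The symptom is present in 35% of the lower-symptom group and in 35% + g of the other. Each group is half the sample at month 0, and the lower-symptom share rises by s at month 9.

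Bias = −s × g.

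Example with g = 20 and s = 20 points:
- month 0: 0.5 × 35 + 0.5 × 55 = 45%
- month 9: 0.7 × 35 + 0.3 × 55 = 41%
- apparent fall: 4 points, with nobody's care changed

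The table gives the apparent fall and, in brackets, the chance of a significant result in a two-sided 5% two-proportion test with 1020 patients per period, ignoring clustering.

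| Gap g | s = 10 | s = 20 | s = 30 |
|---|---|---|---|
| 10 | 1 point (7.5%) | 2 points (15.2%) | 3 points (28.5%) |
| 20 | 2 points (14.9%) | 4 points (44.6%) | 6 points (78.4%) |
| 30 | 3 points (27.3%) | 6 points (77.5%) | 9 points (98.3%) |

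A shift the other way gives a bias of the same size with the opposite sign.

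**4. Does adjustment help?** In 4000 simulated data sets, a Mantel-Haenszel test stratified on the case-mix variable rejected in 5.1% (g = 20, s = 20) and 5.2% (g = 30, s = 20). The unadjusted test rejected in 45.1% and 78.6%. This holds when the variable that shifts has been recorded.

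**5. Single trajectory.** With 15 patients per period, the rejection rate over the same grid stays between 5.0% and 7.7%, because the test has little power. The bias in the estimate is the same as in the table.

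**The case against.** The strongest reply concerns research question 1. The article introduces the terms of the multilevel model as things it will include, not as a closed list, and a covariate list is normally left to an analysis plan. Describing background characteristics is routine, and the sentence does not say that description is their only use. This stands in part: the article does not exclude covariates from the programme model. It does not hold for research question 2, where univariate tests rule out adjustment.

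A reader might infer several stronger points that the documents do not support:
- *The shift is predictable and favours the programme.* No document gives its direction or size. The stated eligibility criteria are the same in both periods, which limits drift without excluding it.
- *The selected best practices change who counts as palliative.* PaTz is offered as an example of Dutch best practices; the list of nine selected ones is in Additional file 1, which is not shown. The Signal box is described as "a tool that enables nursing assistants to identify palliative care needs in their patients". It finds needs in existing patients and is not said to change who is counted.
- *The mechanism applies to all respondents.* Relatives enter through a death, not through a patient being recognised as palliative. They make up 4080 of 2040 + 4080 = 6120 planned respondents. Their mix can still differ between periods, but for other reasons.

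The paired tests suggest the same people measured twice. Eligibility, recruitment and head count all point the other way. Whether paired tests suit these data is a separate question.

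The authors do acknowledge the uncontrolled setting and look for other contributing factors (research question 3c, Discussion). That search is qualitative and cannot remove bias from an estimate.

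**Conclusion.** The point holds in a limited form. The month-0 and month-9 samples are separate cross-sections, there is no control group, and the analysis as written would carry any case-mix or mode difference into the effect estimate. For the trajectories this is fixed by the choice of univariate tests. For the programme it follows from the terms named, although the wording leaves room to add others.

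The size is unknown. The 1 to 9 percentage points and the rejection rates are illustrations that rest on an assumed 50% starting share, a 35% symptom rate, and shifts and gaps of 10 to 30 points. They ignore clustering and do not quantify the interview/postal mode effect on the CQ Index. They show that a moderate shift could pass for an effect in the pooled analysis, not that one will occur. It would be wrong to conclude that the evaluation is biased towards success.

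**What to change.** In the programme multilevel model, include prespecified case-mix covariates taken from the characteristics already recorded:
- for patients: age, sex, diagnosis, care setting with its interview or postal mode, and disease phase or prognosis if recorded;
- for relatives: age, sex, relationship to the deceased and time since death, with the deceased's diagnosis and care setting where recorded.

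The article does not list what is recorded, so the authors should name the variables. Disease phase matters most if a best practice alters recognition; without it, adjustment would leave much of that shift in place.

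Report the adjusted period difference as the main estimate and the crude one beside it. Tabulate the characteristics by period for the programme and for each trajectory.

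Single trajectories, with 15–20 patients per period, cannot carry a full covariate set. Adjust there for at most one or two key variables such as setting, or give the crude difference next to the case-mix table and label it unadjusted.

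The cost is a change to the analysis text, a replacement for the univariate test in any trajectory that is adjusted, and a small loss of cases with missing covariates. Only measured case mix is removed, and the report should say so.
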